## Abstract

**Background:**

Coronary heart disease (CHD) represents approximately 13% of deaths worldwide and is the leading cause of death in the UK with considerable associated health care costs. After a CHD event, timely cardiac rehabilitation optimises patient outcomes. However, a high percentage of these services do not meet necessary performance indicators such as course length and follow-up attendance. Uptake of such services is only 50% in UK patients and support provided 12 months after an event is often limited. To delay and prevent further CHD events leading to hospitalisation, supplementary self-management strategies such as group education, are necessary.

**Methods:**

This is a single-centre, randomised controlled trial (RCT) recruiting participants (*n* = 290) aged ≥18 years who are 12 to 48 months post diagnosis of a CHD-related cardiac event (myocardial infarction, angina and any other acute coronary syndrome). The study aims to implement a structured education programme, with text-message support over 12 months, and identify whether delivery of the programme, to individuals who have a history of a cardiac event, would be an effective and cost-effective strategy for increasing walking. The primary outcome, objectively measured average daily physical activity, specifically step count through walking activity, is assessed using the wrist-worn GENEActiv accelerometer at baseline, 6 and 12 months. Secondary outcomes at 12 months include cardiovascular risk factors such as smoking status, blood pressure, lipid profile, glycated haemoglobin (HbA1c), obesity, self-efficacy, quality of life, physical activity and physical function.

Participants are randomised to either the control group receiving standard care and a physical activity information leaflet, or the intervention group whose partcipants receive the leaflet and are invited to attend two group-based structured education sessions. These encourage participants to adopt and maintain healthy behaviours and self-manage their lifestyle. They are delivered approximately 2 weeks apart by trained facilitators and reinforced via subsequent text-message support.

**Discussion:**

To our knowledge, this is the first trial designed to assess the effectiveness of a group education programme 12 to 48 months after a CHD event diagnosis. If successful, the PACES programme could be translated into effective post-operative cardiac care and complement the current post-operative services available.

**Trial registration:**

ISRCTN, ID: ISRCTN91163727. The trial was registered on 27 February 2017.

**Electronic supplementary material:**

The online version of this article (10.1186/s13063-018-2923-x) contains supplementary material, which is available to authorized users.

## Background

Cardiovascular disease (CVD) is the number-one cause of death globally representing 31% of all global deaths, with coronary heart disease (CHD) representing approximately 13% of deaths worldwide (7.4 million) [1]. CHD-related mortality in the UK accounts for one in six men and more than one in ten women [2]. Health care costs are considerable with nearly £2 billion per year spent on the treatment of CHD [3]. Whilst UK mortality rates from CHD have been decreasing since the 1970s, they are still relatively high compared to other countries in Western Europe [3, 4].

After a CHD event, the risk of further CHD events is greatly increased compared to the general population, unless there is intensive management of CHD risk factors including physical activity, smoking, diabetes, hypertension, hyperlipidaemia and obesity [5]. Following a CHD event, as per the UK National Service Framework, patients are offered a structured education and exercise programme of cardiac rehabilitation (CR) typically at 4 weeks after an acute cardiac event, after which risk factor management is usually transferred to primary care [6].

The UK National Audit of Cardiac Rehabilitation Annual Statistical Report 2016 [7] has compared current national figures with CR delivery recommendations. The current European guidance suggests that such services should be 12 weeks in duration and delivered soon after the cardiac event in order to promote long-term self-management [8]. Currently, the median duration of such programmes in the UK is 9 weeks [7]. At present only 50% of UK patients uptake CR multidisciplinary services [7]. Furthermore, even for those who have attended CR, support is limited thereafter [9]. To delay and prevent further CHD events leading to hospitalisation and potentially death, supplementary strategies are necessary.

### Physical activity in the prevention of subsequent CHD events

Performing physical activity regularly is independently associated with a decrease in CHD risk, which elicits a positive dose-related response on cardiovascular risk factors and should be a predominant focus in both primary and secondary care [10]. Individuals with CHD benefit significantly from physical activity, with higher fitness levels predicting lower mortality rates and CHD-associated complications [11]. The large multi-centre NAVIGATOR trial demonstrated that subsequent risk of a cardiovascular event is inversely associated with both baseline levels and change in ambulatory activity in individuals at high CVD risk [12]. Specifically, an increase or decrease in daily ambulatory activity of 2000 steps between baseline and 12 months was associated with an 8% higher or lower CVD event risk, respectively [12]. These data strongly support interventions that increase physical activity in high-CVD-risk patients.

Previous UK studies have shown benefits in a number of physical activity parameters through structured education and physical activity [13, 14]. Let’s Prevent, a large NIHR-funded randomised controlled trial (RCT), extensively evaluated the implementation of a structured education programme in people at increased risk of developing type 2 diabetes and showed improvements in step count and sedentary time [14]. The MOTION study, which looked at effects of structured exercise in non-diabetic subjects 12–24 months after bariatric surgery, has shown benefits in improved physical activity, weight and functional performance; specifically, the Incremental Shuttle Walk Test (ISWT) [13]. The ISWT is a valid field test of fitness in patients undergoing conventional CR. Following cardiac rehabilitation 62% of patients achieve the minimum clinical difference of > 70 m [7].

After completing CR, patients are encouraged to self-manage their condition and to pursue a healthy lifestyle. Patients’ long-term management plan should be a collaboration between the patient and primary and secondary care services [8]. The National Service Framework for CHD (2000) states that 1 year after cardiac rehabilitation, at least 50% of patients should be undertaking 30 min of moderate physical activity at least five times a week, maintaining a Body Mass Index (BMI) of less than 30 kg/m^2^, and not smoking. UK National Audit figures for 2011–2012 showed that 12 months after cardiac rehabilitation there was a 14% increase in exercise levels, a 1% reduction in BMI in patients with a BMI < 30 kg/m^2^, and a reduction in smoking of 4% [15]. Physical inactivity accounts for 76% of England’s cardiac rehabilitation population upon referral to cardiac rehabilitation [16], and there is a 30% increase in individuals meeting the physical activity guidelines of 150 min per week after completing cardiac rehabilitation [7]. It is well noted that timely cardiac rehabilitation optimises patient outcomes; however, patient support is limited after discharge back to primary care [9].

### Lifestyle education and remote text-message support

Research suggests that inadequate support is available after the initial 12-month period post cardiac event, with half of patients not taking up post-operative support offered. Regular face-to-face contact with health care professionals is expensive and time-consuming and cost-effective strategies to deliver interventions are urgently required in the UK. The delivery approach of behaviour change and self-management education for chronic diseases, such as CHD, should be directly relevant to primary care pathways [17]. It is recognised that structured education is a method of promoting self-management in clinical populations, specifically those with CHD, and that ambulatory physical activity positively affects future cardiovascular event risk [18].

With the advent of increasingly sophisticated mobile phone technology, text messaging has been used to deliver health education messages which reinforce and promote behavioural change. Whilst some studies suggest that text-message reminders of health education and medication are not beneficial in terms of self-efficacy [19], others have demonstrated that it can be used effectively to reduce CHD risk; for example, by preventing type 2 diabetes [20], increasing levels of leisure-time physical activity and walking [21], or adherence to antiplatelet therapy [22]. A recent mixed-methods observational cohort study of automated text messaging and remote nursing as part of mobile phone diabetes programmes demonstrated improvements in the taking of medications, healthy eating, foot care, exercise, and glucose monitoring as well as self-efficacy, social support, and health belief measures [23]. In this study, behavioural theory was used to inform, identify and evaluate efficacy of the mobile phone intervention.

It is apparent, given the above factors, that more support 1 year after a cardiac event is needed to complement current services. There is a need to develop and evaluate a structured education programme focusing on lifestyle factors, such as physical activity, for individuals who have a history of a cardiac event.

## Methods

### Aims and objectives

To implement an acceptable and effective structured education programme with text-message support for increasing total daily physical activity, specifically walking activity measured using accelerometry, and reducing subsequent cardiovascular events in individuals 12 to 48 months after diagnosis of a cardiac eventTo assess the effectiveness of a structured education intervention to improve cardiovascular risk factors such as smoking, blood pressure, lipid profile, obesity, self-reported physical activity and objectively measured physical activity intensityTo assess the acceptability, uptake and feasibility of implementing the programme in a population at high future risk of another CVD event in primary care

### Study overview

This single-centred, two-arm, parallel, 12-month RCT co-ordinated from the University Hospitals of Leicester NHS Trust compares structured disease management education, delivered as a group education programme followed by text-message support, with usual care. The Physical Activity after Cardiac EventS (PACES) education programme has been designed according to the Medical Research Council guidelines for developing and evaluating complex interventions in health behaviour change programmes, along with Michie et al*.* and the NICE guidelines, to inform behaviour-change techniques [24–26]. The main goal of the PACES programme is to increase physical activity; specifically, walking activity. Figure 1 describes the study flow and participant progression through the PACES study. The trial is sponsored by the University of Leicester and approval was granted by the West Midlands – Solihull Research Research Ethics Committee and the UK Health Research Authority. The study was prospectively registered (ISRCTN91163727). The protocol is reported according to the Standard Protocol Items: Recommendations for Interventional Trials (SPIRIT) guidelines; see Fig. 2 and Additional file 1.

**Fig. 1 Fig1:**
[figure not shown]
Flowchart of research procedures

**Fig. 2 Fig2:**
[figure not shown]
Standard Protocol Items: Recommendations for Interventional Trials (SPIRIT) diagram. Abbreviations: *ISWT* Incremental Shuttle Walk Test, *HbA1c* glycated haemoglobin, *HADS* Hospital Anxiety and Depression Scale, *RPAQ* Recent Physical Activity Questionnaire

### Participant invitation and recruitment

Participants are identified 12–48 months after a CHD cardiac event diagnosis from the University Hospitals of Leicester cardiology department and phase 4 community-based cardiac rehabilitation providers. Phase 4 cardiac rehabilitation typically refers to community-based cardiac rehabilitation, which provides people with known coronary heart diseases (myocardial infarction, coronary artery bypass graft, percutaneous coronary intervention and stable angina), the possibility to benefit from weekly supervised exercise sessions. People who are eligible for phase 4 cardiac rehabilitation include those who have participated in a 6–12-week cardiac rehabilitation programme. Phase 4 is often referred to as a maintenance programme and is only available to those who meet certain medical criteria and have been assessed by their general practitioner (GP).

Potential participants identified as living in Leicestershire and within the post-CHD event diagnosis window (12–48 months) are invited to participate by postal invitation. The postal invitation includes an invitation letter and a short version of the participant information leaflet. A follow-up telephone call is made to non-responders to check that they have received the invitation and ask if they have any questions relating to the PACES study and its procedures. All positive responders to the postal invitation receive telephone screening related to the inclusion and exclusion criteria and are provided with an opportunity to ask questions related to the study. All potential participants who pass the telephone screening phase are invited to visit 1 to ensure that they meet the practical elements of the inclusion and exclusion criteria. If deemed able and eligible to participate, written informed consent is obtained after which baseline assessment measurements are carried out (Table 1) and randomisation takes place. Ahead of visit 1, the potential participant receives an appointment confirmation letter and the PACES full participant information leaflet. These visits take place at University Hospitals of Leicester premises or in community hospitals where appropriate resuscitation facilities are available.

**Table 1 Tab1:** Screening, primary and secondary outcome measures

	Measurement type	Measurement (units)	Baseline	6 months	12 months
Screening	Demographic data	Date of birth, age, gender, ethnicity,	x		
		smoking status, alcohol status employment status	x		x
	Health history	Type of cardiac event defining as eligible, date of CHD diagnosis,	X		
		medical history and medications, whether family history of CHD	x		x
Primary outcome measure	Physical activity	Accelerometer (average daily physical activity - milli-gravitational units (mg))	x	x	x
Secondary outcome measures	Aerobic fitness	Incremental Shuttle Walk Test (metres)	x		x
	Anthropometric	Height (cm) and body mass (kg)	x		x
		Body Mass Index (kg/m^2^)			
		Waist circumference (cm)			
		Hip circumference (cm)			
		Waist to hip ratio			
	Cardiovascular	Blood pressure (mmHg) and resting heart rate (bpm)	x		x
	Blood samples (all non-fasting)	Lipid profile (cholesterol, HDL, LDL, triglycerides)	x		x
		HbA1c (mmol/mol, %)			
	Questionnaires	Jenkins Self-efficacy for Exercise Expectations Scale [45]	x	x	x
		Hospital Anxiety and Depression Scale (HADS) [58]	x	x	x
		MacNew Heart Disease [43, 44]	x	x	x
		Recent Physical Activity Questionnaire (RPAQ) [40]	x	x	x
		EuroQoL (EQ-5D-5L) health-related quality of life instrument [43, 44]	x	x	x
		Morningness-Eveningness Questionnaire [49, 50]	x		
Exploratory endpoint	Stored serum and plasma samples	Biomarkers of inflammation, proteomics, metabolomics and novel markers of cardiovascular health	x		x

*CHD* coronary heart disease, *HbA1c* glycosylated hemoglobin, *HDL* high-density lipoprotein, *LDL* low-density lipoprotein

### Eligibility criteria

To be eligible for the PACES study individuals must meet the following criteria:Aged 18 years or olderBe 12–48 months post confirmed diagnosis of a cardiac event (myocardial infarction, angina or acute coronary syndrome)Able to speak and read English in order to participate effectively in a group education programmeWilling and able to attend the education sessions and clinic visitsWilling and able to give informed consentAccess to a mobile phone in order to receive text messagesWilling to allow their GP notification of their participation in the study and access to patient records for purpose of the studyAble to take part in moderate physical activity as assessed using the ISWT (level 3 or above (120 m)) [27]

Individuals will be excluded from the PACES study if they have/are:A diagnosis of heart failure where the underlying primary cause is not myocardial disease as a result of atherosclerosisMusculoskeletal limitations that limit physical activity (e.g. musculoskeletal injury)Participating in another clinical intervention study or have done so in the past 12 weeksA severe life-threatening co-morbidity (e.g. malignancy)Poor exercise capacity, (< level 3 on the ISWT (120 m)) [27]Housebound or immobileUnstable symptoms (chest pain or breathlessness at rest; unstable stage II hypertension (160/100 mmHg), not on necessary medications)

### Algorithm for exclusion of individuals with poor exercise capacity and unstable symptoms

All individuals who display a potential risk if they were to increase their physical activity levels are screened out using the unstable symptom check or ISWT and referred to the necessary support networks in primary or secondary care. This is to ensure that complications or symptoms they are experiencing are addressed.

### Randomisation

Upon completion of visit 1, participants are randomised using a 1:1 block design and stratified by gender (men; women) and ethnicity (White European; other) to receive either standard management in primary care or to a complex intervention with group-based structured education and text-message support. An exception is made for people living in the same household, where in the unlikely event of this occurring the second person is not randomised but is allocated to the same arm as the first person. This is to prevent contamination between people living in the same household but randomised to different arms. The randomisation schedule and list was developed by an independent statistician and allocation of randomisation is carried out by a researcher independent of the team. Participants are informed of their randomisation allocation once visit 1 is completed, ahead of their 6 and 12 months’ follow-ups. As the intervention is a group education programme the participants cannot be blinded to the randomisation. The research nurses collecting the follow-up data are not informed of the randomisation of the participant but it is possible that the information is passed onto them by the participant.

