### Treatment regimens

#### Control group

Control group participants are provided with general health advice in the form of a standard British Heart Foundation information leaflet after visit 1, and are returned to standard care delivered by their GP. The information leaflet entitled ‘*Put Your Heart into Walking*’ describes walking as a fitness activity to keep your heart healthy [28].

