### Primary outcome

The primary outcome measure is change in objectively measured ambulatory activity from baseline to 12 months using the GENEActiv wrist-worn, tri-axial accelerometer (GENEActiv model 1.1, ActivInsights Ltd., Kimbolton, UK) with a dynamic range of ± 8 g, where g is equal to the earth’s gravitational pull. Increasing physical activity is an important behaviour to adopt after a cardiac event illustrating why objective ambulatory activity has been selected as the primary outcome. Participants are asked to wear the GENEActiv accelerometer on their non-dominant wrist for eight consecutive days (24 h) (wearing the monitor from the date of the assessment visit or from a specified date when sent in the 6-month postal follow-up). The accelerometer is configured to collect data at 100 Hz and records total physical activity, which includes light, moderate, vigorous and moderate to vigorous physical activity (MVPA), sedentary behaviour and sleep in milli-gravitational units (mg). Participants are also asked to complete a log whilst wearing the monitor to provide their waking hours and wear-time information. An appropriately trained individual instructs the participant on correct placement of the monitor using the SOPs. Participants are given a stamped addressed envelope to return the monitor once completed. Upon return the data are downloaded to a computer using the software supplied by the manufacturer and are then ready for analysis. The accelerometers are processed by staff blinded to the intervention group allocation.

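### The eight-day baseline accelerometer wear starts on the date of visit 1, but allocation is made and disclosed when that visit ends, so much of the primary outcome's baseline may be recorded by participants who know their arm

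*Protocol article*

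**What the plan says.** Four places in the protocol article bear on the order of events.

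- **Randomisation.** "Upon completion of visit 1, participants are randomised using a 1:1 block design". Disclosure has the same trigger: "Participants are informed of their randomisation allocation once visit 1 is completed, ahead of their 6 and 12 months’ follow-ups". The section also accepts that participants are not blinded: "As the intervention is a group education programme the participants cannot be blinded to the randomisation".
- **Primary outcome.** The monitor is worn round the clock for eight days in a row, and the start is defined as "wearing the monitor from the date of the assessment visit or from a specified date when sent in the 6-month postal follow-up". The recording finishes at home: "Participants are given a stamped addressed envelope to return the monitor once completed".
- **Control group and Intervention group.** Controls receive the "standard British Heart Foundation information leaflet after visit 1". The intervention arm receives the same leaflet, also after visit 1.
- **Participant invitation and recruitment.** Here the order is consent, then the baseline measures of Table 1 (which include the accelerometer), then randomisation.

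The Primary outcome section defines the outcome as change from baseline to 12 months. Under Primary outcome data processing and data analysis, the model also adjusts for baseline activity and for the change in wear-time from baseline. All of these use the same baseline week.

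**The concern.** A baseline covariate is safe to adjust for because allocation cannot have influenced it. That protection is lost if participants learn their arm during the recording, and more so when the outcome is a behaviour they can change at will. Someone told they will join a walking programme may start early. A control may be disappointed, or may compensate. Either reaction would enter the baseline differently in the two arms, and the primary model would then subtract part of it from the treatment effect or add to it.

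The planned sensitivity analyses (per-protocol, multiple imputation, restriction to education within 2 months) are not described as dropping the baseline, so they would not be expected to reveal the problem.

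**Working it through.** **1. The plan's own figure.** Inputs from Sample size: difference 2.1 mg, SD 5.3 mg, power 80%, significance level 5% (two-sided, from Data analysis). The normal approximation gives 2 x (1.960 + 0.842)^2 x (5.3/2.1)^2 = 100 per arm. The exact two-sample t-test gives 100.96, so 101 per arm and 202 in total, as stated. Allowing for 30% loss, 202/0.70 = 288.6, which is consistent with 290. The sample size reproduces and this point does not change it.

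**2. Order of events.**

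| Event | Timing given |
|---|---|
| Baseline wear starts | Date of visit 1 |
| Randomisation | On completion of visit 1 |
| Disclosure | Once visit 1 is completed; only outer limit is before the 6- and 12-month follow-ups |
| Leaflet, both arms | After visit 1; day not fixed |
| Baseline wear ends | Eight days after it starts, then postal return |

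Visit 1 is an attendance at hospital premises (Participant invitation and recruitment), so it ends long before an eight-day recording does. If randomisation and disclosure happen on the visit date, about 7 of the 8 days follow them. The order in the recruitment section therefore cannot be met for the accelerometer unless allocation waits, and no section says that it does.

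**3. Effect on the estimate.** Let b be the within-arm slope of 12-month activity on baseline. Let s be the shift in the intervention arm's baseline, relative to control, caused by knowing the allocation. The adjusted estimate is

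(difference at 12 months) - b x (difference at baseline),

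so its expected value is 2.1 - b*s when the true effect is 2.1 mg. Modelling change instead of the 12-month value, with baseline as a covariate, gives the same arm coefficient. A slope of b = 1 corresponds to a plain comparison of change scores.

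The documents give neither b nor s, so these are assumed ranges:

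| s (mg) | b = 0.5 | b = 1.0 |
|---|---|---|
| 0.2 | 2.00 | 1.90 |
| 0.5 | 1.85 | 1.60 |
| 1.0 | 1.60 | 1.10 |

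A negative s of the same size adds the same amount: at s = -0.5 mg the estimate is 2.35 to 2.60 mg.

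**4. Scale of s.** The protocol equates 2.1 mg with about 30 min of light walking. Scaling in proportion, 0.5 mg is 30 x 0.5/2.1 = about 7 min a day averaged over the recording, and 1.0 mg is about 14 min.

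**5. The leaflet.** If it raises baseline activity by the same amount c in both arms, the baseline difference between arms changes by c - c = 0. It alters the level of the baseline, and hence within-arm change, but not the contrast.

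**The case against.** The strongest defence is that the text is unclear rather than wrong. The recruitment section puts baseline measures first. Disclosure and the leaflet have no fixed day. Allocation is carried out by a researcher independent of the team, so same-day notice cannot be assumed, and the flowchart and SPIRIT schedule are not visible here. Little of the programme itself need reach the baseline week: education has a target of within 2 months of recruitment, the pedometer comes with it, and text messages follow the second session. All of this stands. It limits the point to knowledge of allocation, with an effect of unknown size and direction. It does not show that the week is protected.

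A reader might infer several stronger things that the documents do not support:

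- **That the baseline week starts after randomisation, disclosure and the leaflet.** Wear starts on the visit date, so it may begin first. The overlap is with the rest of the week.
- **That the leaflet biases the comparison.** Both arms get it, so a common shift cancels.
- **That using the baseline twice doubles the bias.** With baseline as a covariate, subtracting it as well changes nothing in the arm coefficient.
- **That a definite loss of power follows.** Take b = 0.7 and s = 0.5 mg, giving 1.75 mg. With the unadjusted standard error, 5.3 x sqrt(2/101) = 0.746, power is about 65%. But a slope of 0.7 implies an adjusted analysis. If 5.3 is the SD of change, variances are equal and the correlation is 0.7, the residual SD is sqrt[5.3^2/(2 x 0.3) x (1 - 0.7^2)] = 4.9 and the standard error about 0.69. Power is then about 72%. Only the shift in the estimate is robust to this choice.

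Failed baseline recordings are at least partly provided for, by the 10% allowance for monitor non-compliance and the planned imputation analysis. They are not part of this point.

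**Conclusion.** The point holds in this form: the stated timings allow most of the primary outcome's baseline to be recorded after unblinded participants know their arm, and they conflict with the order given in the recruitment section. It does not establish that this happened to every participant, or that the result is biased.

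The possible bias is -b*s. At an assumed shift of 0.5 mg and a slope of 0.5 to 1.0 it is 0.25 to 0.5 mg, or 12% to 24% of the 2.1 mg target, in either direction. The shift of 1.0 mg is hard to credit from knowledge of allocation alone, since it is nearly half the effect sought from the whole programme. Because the target is small and the remedy cheap, this is worth correcting rather than only clarifying.

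**What to change.** **Remaining recruits.** Randomise only after the baseline wear period has ended, preferably once the monitor is back. At the least, hold disclosure of allocation and the leaflet until then; the bias comes from participants knowing their arm, so withholding that knowledge is enough. Amend the Randomisation, Primary outcome, and Participant invitation and recruitment sections so that they give one order of events. If practice already protects the baseline week, say so there.

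**Participants already randomised.** Record the dates of randomisation, disclosure and wear, and report how many baseline days followed disclosure in each arm. Add a sensitivity analysis comparing 12-month ENMO between arms, adjusted for the stratification factors only, which leaves out both baseline activity and the change in wear-time.

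**Cost.** A protocol amendment, and a delay of one to two weeks in telling participants their allocation. Recruitment was expected to finish by the end of March 2018, so the change may reach only some participants; the dates and the sensitivity analysis cover the rest. The sensitivity analysis is less precise: dropping a baseline with correlation r to the outcome widens the standard error by 1/sqrt(1 - r^2), which is 1.15 at an assumed r of 0.5 and 1.40 at 0.7. It should therefore support the primary analysis rather than replace it. Repeating the wear after a failed file is optional and not needed for this fix.
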